**3.6. Project Funding***

Is this project funded by or associated with a grant or contract?

Yes

**Selected Proposals**

Proposal No. 10032353

**Title**

Implementation of Prolonged Exposure in the Army: Is Consultation Necessary for Effective Dissemination?

**Sponsor Funding**

*Is this study funded by an industry sponsor?*

No

**4.2. Management of Information for Multi-Center Research**

Reporting unanticipated problems involving risks to participants or others (UPIRSOs): The identified risk to both mental health providers and patients seeking treatment is the risk of breach of confidentiality. UPIRSOs will be submitted to the IRB within 10 working days of discovery, or as directed by the local IRB. There is no plan for an interim data analysis or report. Protocol modifications will be accomplished through amendments to the approved protocols at the local sites as well as the University of Pennsylvania. The Penn study staff will draft any needed modifications. Collaborators at the University of Texas Health Science Center San Antonio (UTHSCSA) will coordinate the submission of regulatory documents including protocol amendments to the military IRBs. The Penn study staff will submit regulatory documents including protocol amendments to the Penn IRB. Communication between Penn and the performance sites: The Penn investigators will hold regular teleconferences with the performance sites to monitor study progress, identify any adverse events and protocol deviations, communicate any changes or modifications to the study protocol, and problem solve with the site staff. Additionally, Penn investigators will make annual visits to the performance sites to conduct training and provide on-site consultation and monitoring.

**5. Protocol**

*5.1. Abstract*

This study will examine how evidence-based therapies (EBTs), such as Prolonged Exposure (PE) for posttraumatic stress disorder (PTSD) can be successfully disseminated and implemented in the Army by comparing two PE training models: Standard PE training (workshop only) and Extended PE training (workshop plus consultation). Two hundred (200) mental health providers at three medium-to large CONUS Army installations will be randomly assigned to either Standard PE training or Extended PE training. All providers will receive a 4-day PE workshop, along with the distribution of training materials and treatment manuals, conducted at the military site by the Overall Study PI, [name], and her team. Following the 4-day workshop, participants randomized to the Extended PE training will receive weekly phone consultation with a PE expert on two PE therapy cases followed by twice monthly telephone consultation as needed for six months. Participants randomized to the Standard PE training group will not receive any additional consultation following the workshop. Providers will not be required to use PE therapy to treat their patients with PTSD; using PE will be optional. A major outcome of this study is the proportion of the providers PTSD patients that are offered PE. The mental health outcomes of providers PTSD patients will also be monitored as a second major outcome. Patients seeking care for PTSD from participating providers will be recruited, consented and offered treatment for PTSD and related problems to prospectively and systematically assess what type of treatment they are offered and their response to treatment.

*5.2. Objectives*

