**Protocol Number:** 818540

**Principal Investigator:** [name]

**Protocol Title:** Implementation of Prolonged Exposure in the Army: Is consultation necessary for effective dissemination?

**Short Title:** The Post-Traumatic Stress (PTS) Study

**Protocol Description:** This study will examine whether Prolonged Exposure (PE) for posttraumatic stress disorder (PTSD) can be successfully disseminated and implemented in the Army. 120 mental health providers will attend a 4-day PE workshop and will receive in-depth case consultation or no additional consultation following the workshop. Providers will complete surveys about their therapy practices. Patients seeking care for PTSD from providers will be recruited and consented to assess treatment response.

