**2.4. Method for Assigning Subjects to Groups**

The study proposes to enroll approximately 100 participants in each condition. Participants will be randomized to conditions by a computer-based random list generator.

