**6. Study Design**

**Phase***

Not applicable

*6.1. Design*

This is a randomized clinical trial comparing two methods of training mental health providers in Prolonged Exposure (PE) treatment for Posttraumatic Stress Disorder (PTSD). Two hundred (200) mental health providers at three medium-to-large CONUS Army installations will be randomly assigned to either Standard PE training or Extended PE training. All providers will receive a 4-day PE workshop, along with the distribution of training materials and treatment manuals, conducted at the military site by the Overall Study PI, [name], and her team. Following the 4-day workshop, participants randomized to the Extended PE training will receive weekly phone consultation with a PE expert on two PE therapy clinical cases followed by twice monthly telephone consultation as needed for six months. Participants randomized to the Standard PE training group will not receive any additional consultation following the workshop. Providers will not be required to use PE therapy to treat their patients with PTSD; using PE will be optional. A major outcome of this study is the proportion of the providers PTSD patients that are offered PE. The mental health outcomes of providers PTSD patients will also be monitored as a second major outcome. Patients seeking care for PTSD from participating providers will be recruited, consented and offered treatment for PTSD and related problems to prospectively and systematically assess what type of treatment they are offered and their response to treatment.

*6.2. Study duration*

The study is expected to start in May 2014 and end in May 2017. Subject recruitment and data collection will mostly occur in years 2, 3, and 4. Data analysis will occur in year 4.

*6.3. Resources necessary for human research protection*

Describe research staff and justify that the staff are adequate in number and qualifications to conduct the research. Describe how you will ensure that all staff assisting with the research are adequately informed about the protocol and their research related duties. Describe access to a population that would allow recruitment of the targeted number of subjects. If medical or psychological services as a consequence of the research, describe how the subject will be referred to those services. Describe your facilities and justify that the facilities are adequate. Verify that there is sufficient time to conduct and complete the research.

*6.4. Research Staff*

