**Subjects enrolled by Penn Researchers**

0

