**Subjects enrolled by Collaborating Researchers**

120

*7.2. Accrual*

Provider-participants: The On-Site PI will present information about the study and participation to all mental health providers who provide psychotherapy at each site. Those who meet the inclusion and exclusion criteria will be invited to participate in the study and provided informed consent. The project coordinator and research assistant at each site will assist with the coordination of recruitment, screening, and informed consent of participants.

Patient-participants: Patients who screen positive for PTSD according to the PCL-5, PCL-C, or whichever screening measure is used as the performance site’s screening tool for PTS, and who are assigned to one of the provider-participants enrolled in the study will be invited to participate in the study and will meet with a member of the research team to review informed consent. Patients who consent to the study will complete a baseline evaluation with a BOA that includes the CAPS, the M.I.N.I, and self-report questionnaires.

*7.3. Key inclusion criteria*

Key inclusion criteria for provider-participants are the following:

- Male and female mental health providers whose job duties include providing psychotherapy to adult patients, ages 18-65, seeking treatment for PTSD.

- 20% of expected patient caseload with trauma related difficulties

- Support from local leadership to ensure that providers are granted the time and resources necessary to participate in study activities, including providing 90-minute once weekly sessions, time off to participate in the training workshop, time to participate in consultation , time to complete study assessments, etc.

Key inclusion criteria for patient-participants are the following:

- Male and female patients aged 18-65 who are seeking treatment from one of the mental health providers participating in this study.

- Clinically significant PTSD symptoms, defined as a severity score of 25 or greater on the Clinician-Administered PTSD Scale for DSM-5 (CAPS-5).

*7.4. Key exclusion criteria*

Key exclusion criteria for provider- participants are the following:

- Definite plans to terminate their position or relocate from the Army base at some point during the 1 year following training.

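### The protocol gives two sizes for the randomised provider sample, 120 and 200, and nothing in it shows which is current

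*Protocol*

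**What the plan says.** Five places in the protocol bear on the number of providers.

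- Protocol Description (opening page): "120 mental health providers will attend a 4-day PE workshop and will receive in-depth case consultation or no additional consultation following the workshop".
- Section 2.4, Method for Assigning Subjects to Groups: "The study proposes to enroll approximately 100 participants in each condition". Section 2.5 has every participant attending the workshop, so the participants meant here are providers.
- Section 5.1, Abstract: "Two hundred (200) mental health providers at three medium-to large CONUS Army installations will be randomly assigned".
- Section 6.1, Design: "Two hundred (200) mental health providers at three medium-to-large CONUS Army installations will be randomly assigned".
- Enrolment counts printed between sections 7.1 and 7.2: the entry headed "Subjects enrolled by Penn Researchers" is 0 and the entry headed "Subjects enrolled by Collaborating Researchers" is 120. Neither heading says providers.

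Sections 5.1 and 6.1 add that all the providers receive the workshop. The protocol shows no sample-size calculation, dropout rate or evaluable number. That absence is not the point here, since such detail may sit in a statistical analysis plan that is not at hand.

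**The concern.** The number of randomised units is a figure the trial relies on, and the protocol states it in two incompatible ways. Section 5.2.2 makes provider behaviour and provider attitudes the primary outcomes, so the provider count is the sample size for the primary comparison. The protocol's question is whether the costlier training with consultation is needed on top of a workshop (section 5.3). Anyone judging how much a difference, or the lack of one, can say about that needs to know which size was planned. The sites and the ethics boards work from this document and cannot tell from it whether the target is 120 or 200.

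**Working it through.** **1. Do the figures describe the same thing?** The Protocol Description's 120 are providers who attend the workshop and then receive consultation or none. The 200 in sections 5.1 and 6.1 are providers who are randomised, all of whom receive the workshop. Same population, same stage. Section 2.4 agrees with 200: about 100 × 2 conditions = about 200.

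**2. Size of the gap.** 200 − 120 = 80. As a share of 200: 80/200 = 40%. As a share of 120: 80/120 = 67%.

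**3. Can the text bridge the gap?**
- Rounding: 120 split equally is 60 per arm, which an approximate 100 cannot cover.
- Attrition: 200 × (1 − 0.40) = 120, so a 40% loss would be needed. No loss rate is stated, and the 120 are counted at the workshop, not at the end of follow-up.
- Sites: sections 5.1 and 6.1 place all 200 at the three installations, and the coordinating university enrols 0, so no other source supplies the missing 80.
- Enrolment counts: 0 + 120 = 120 subjects. If these are providers only, they match the Protocol Description. If they also include patients, the number of providers is below 120 and the conflict with 200 is larger.

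**4. Reproducing 120 or 200.** Not possible. The protocol gives no significance level, power, effect size, standard deviation or dropout rate, so neither number can be derived and neither is favoured.

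**5. Effect on precision.** For a difference between two equal arms of n each, the standard error is SD × sqrt(2/n). The ratio of interval widths is sqrt(100/60) = sqrt(200/120) = 1.29, or 29% wider at 120. This ratio does not depend on the significance level, the power or the SD. It needs only the same allocation, the same fractional loss and the same model at both sizes.

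95% half-widths in SD units, 1.96 × sqrt(2/n):
- n = 100: 1.96 × 0.1414 = 0.28
- n = 60: 1.96 × 0.1826 = 0.36

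**6. Illustration of the detectable difference.** Assumed, not taken from the protocol: two-sided 5%, 80% power, equal arms, unadjusted two-sample t-test, no dropout. The normal approximation is (1.960 + 0.842) × sqrt(2/n) = 2.802 × sqrt(2/n).

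| Providers per arm | Normal approximation | t-test |
|---|---|---|
| 100 | 0.396 SD | 0.398 SD |
| 60 | 0.511 SD | 0.516 SD |

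On the same assumptions, an effect of 0.398 SD has 80% power with 100 per arm and 58% with 60 per arm.

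**The case against.** Several stronger conclusions are tempting and do not hold.

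- **That 120 providers is stated twice.** Only the Protocol Description says so outright. The enrolment counts say subjects, and section 7.1 defines two groups of participants, providers and patients. Reading the 120 as providers is likely, because it matches the Protocol Description, but it is an inference.
- **That the precision is undefined, or that the design in sections 2.4, 5.1 and 6.1 does not exist.** The arms, sites and randomisation are the same at either size. What is left open is which of two sizes applies.
- **That 120 is the true number, so a null result would be over-read.** The document does not show which figure is current, and it claims no power or detectable effect for 200 against which a null result could be misjudged. Nor does it tie the figure to a rule for ending enrolment or to the length of the randomisation list.
- **That 0.40 and 0.52 SD are the trial's detectable differences.** Section 8.2 plans t-test contrasts, but its main analysis is mixed-effects regression with repeated measures and baseline covariates, which could detect smaller differences. The split of 120 into 60 and 60 is also assumed. Turning these values into percentage points of treatment use would need an SD that the protocol does not give.

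All of these limits stand, and they narrow the claim to the inconsistency and its consequence for precision. None of them reconciles 120 with 200. An unseen analysis plan might justify one of the numbers, but it would not remove the other from the protocol.

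**Conclusion.** The point holds as an internal inconsistency in a figure the trial relies on, and it needs correcting. The randomised provider sample is 120 in the Protocol Description, with a matching count of 120 subjects in the enrolment entries, and 200 in sections 5.1 and 6.1, with about 100 per condition in section 2.4. The difference is 80 providers, or 40% of the larger figure. Precision is therefore ambiguous between two values whose confidence intervals differ in width by about 29%. That figure assumes equal allocation and the same model and fractional loss at either size. The 0.40 and 0.52 SD values show the scale of the gap under the assumptions in the working; they are not properties of the planned analysis. The document gives no basis for choosing between the two totals, and none is chosen here.

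**What to change.** State one provider total and one per-arm number, and use them in the Protocol Description, sections 2.4, 5.1 and 6.1, and the enrolment counts after section 7.1. Say whether those counts cover providers only. Say whether the other figure was a superseded target, an evaluable number or an error.

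- **If 120 is operative:** restate sections 2.4, 5.1 and 6.1 as 120 in total (60 per arm if allocation is equal) and remove the statement of about 100 per condition. Any power or precision statement made elsewhere should use that number. The cost is wording and a less favourable precision, with no added enrolment.
- **If 200 is operative:** correct the Protocol Description and the enrolment counts. If the counts are of providers only, the collaborators' entry rises by 80. That changes the stated enrolment, not only the wording, and under section 4.2 it goes through amendments at the local sites and the coordinating university.

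The illustrative detectable differences above should not be written into the protocol, because they rest on assumptions made for this check.

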5.2.1. Overall objectives

This study will examine how evidence-based therapies (EBTs), such as Prolonged Exposure (PE) for posttraumatic stress disorder (PTSD) can be successfully disseminated and implemented in the Army by comparing two PE training models: Standard PE training (workshop only) and Extended PE training (workshop plus consultation). We hypothesize that compared to Standard training, the Extended PE training will lead to: 1) Greater frequency of PE delivery; 2) Higher provider self-efficacy and positive attitudes towards PE; and 3) Superior PTSD patient outcomes. The study will answer the following questions: Does Extended PE training lead to significantly greater use of PE than does Standard PE training? Does Extended PE training lead to significantly greater changes in provider attitudes compared to Standard PE training? Does Extended PE training lead to significantly greater changes in PTSD patient outcomes versus Standard PE training?

5.2.2. Primary outcome variable(s)

The first set of Objectives concern provider behaviors, specifically hypothesizing that Extended Training will result in a greater proportion of PTSD patients treated with PE, use of PE with more complex patients (i.e., those with greater severity, complicating factors, and/or comorbidities), and better adherence to the PE protocol in those cases treated with PE. The measures to address this objective will be derived from self-report scales completed after consultation. When feasible, summary measures will be derived by summing items bearing on the same issue. For example, the Implementation Survey includes a 25-item section listing comorbid conditions and complicating factors. The fidelity analysis will be based on ratings by IEs of recorded sessions. Another set of Objectives concerns changes in provider attitudes. The outcome measures will be summary scores derived from the Implementation Surveys, using sums of relevant items as appropriate to operationalize provider self-efficacy, satisfaction and expectations for change.

5.2.3. Secondary outcome variable(s)

The third set of objectives concern changes in patient outcomes, specifically PTSD symptom severity, other symptoms, dropout, and satisfaction with treatment. These measures will be given at baseline and after 8-15 sessions of therapy, or after 5 months since initial assessment, whichever comes first.

*5.3. Background*

The Urgent Need for Effective PTSD Treatment in the Military

The current wars in Iraq and Afghanistan combined with wide implementation of mental health screening and management initiatives in the military have drastically increased the number of active duty soldiers who are identified as needing treatment for military-related trauma, and in particular, treatment for posttraumatic stress disorder (PTSD). An estimated 14% of Operation Iraqi Freedom/Operation Enduring Freedom/ Operation New Dawn (OIF/OEF/OND) military personnel meet criteria for PTSD (Tanelian & Jaycox, 2008). The greatly increased number of soldiers with PTSD has generated an enormous need to provide effective and efficient treatment for this disorder. This need, in turn, calls for a systematic effort to train military mental health providers in how to competently deliver short-term, efficacious, evidence-based treatments (EBTs) for PTSD. Treating PTSD is important not only to ameliorate PTSD symptoms, but also to prevent the devastating process associated with the chronicity of the disorder. Indeed, in the absence of effective treatment, PTSD frequently becomes chronic and comorbid with major depression, other anxiety disorders, substance use disorders (Kessler et al., 2005), poor physical health illnesses (Jakupcak, Luterek, Hunt, Conybeare, & McFall, 2008; Vasterling et al., 2008), and low quality of life (Zayfert et al.,2002).

Advantages of Prolonged Exposure Treatment for PTSD

Fortunately, we have developed highly effective and efficient treatments for PTSD. Among them are exposure therapies, cognitive therapies, and eye movement desensitization and reprcessing (EMDR). Exposure therapies, and in particular prolonged exposure (Foa, Hembree, & Rothbaum, 2007), possess the largest body of empirical evidence for their efficacy (IOM, 2007). Prolonged exposure (PE) is a specific exposure therapy program designed to help PTSD sufferers to emotionally process their traumatic experiences through repeated revisiting and recounting their trauma memories (imaginal exposure), and repeated, gradual confrontation with trauma-related, safe, situations that the person avoids (in vivo exposure). PE comprises three main components: (a) in vivo exposure to trauma reminders, typically as between-session assignments; (b) imaginal exposure to the memory of the traumatic event, both in session and between sessions; and (c) processing of imaginal exposure. Two additional less central components are: (d) psycho-education about the nature of trauma and (e) training in controlled breathing.

As noted above, among the evidence based treatments (EBTs) for PTSD, PE has gained the most empirical evidence for its efficacy. As a result, PE has been identified in the joint VA-Department of Defense Clinical Practice Guideline for PTSD (VA-DoD Clinical Practice Guideline Working Group, 2010) as strongly recommended for use with veterans with PTSD. The 2007 report issued by the Institute of Medicine (IOM) concluded that exposure therapy was the only treatment for PTSD with sufficient evidence for its efficacy. Numerous randomized controlled trials indicate that PE is effective in reducing PTSD symptoms (see Cahill, Rothbaum, Resick & Follette, 2009), and is associated with rapid change and maintenance of treatment gains over time (e.g., Foa et al., 2005; Powers, Halpern, Ferenschak, Gillihan, & Foa, 2010; Taylor et al., 2003). In addition to greatly reducing PTSD symptoms, PE also reduces depression, general anxiety, guilt, anger, and anxiety sensitivity, and improves social functioning and health (Keane, Marshall, & Taft, 2006; Rauch et al., 2010). Moreover, PE is effective in treating PTSD related to a wide range of traumas as well as PTSD in comorbid population, including traumatic brain injury (Rauch, unpublished), alcohol dependence (Foa et al., in preparation), borderline personality disorder (Harned et al., 2012), and major depression (Hagenaars, van Minnen, & Hoogduin, 2010).

Importantly, the efficacy of PE was studied by the greatest number of independent research groups around the world. Compared to other EBTs for PTSD, the techniques used in PE are relatively simple, the manual is highly structured, and the procedures are stream-lined, easy to learn, and straightforward to deliver. Furthermore, several studies have shown that patients prefer exposure therapy over other types of treatment. For example, PE is preferred over medication (among women exposed to trauma: Angelo, Miller, Zoellner, & Feeny, 2008; among women with PTSD: Feeny, Zoellner, Mavissakalian, & Roy-Byrne, 2008), and over other EBTs for PTSD (Becker, Darius, & Schaumberg, 2007). Thus, PE has many characteristics of the optimal candidate for widespread dissemination: it is effective with a wide range of PTSD sufferers, it is relatively easy to learn and deliver, and it is the preferred treatment type among patients.

The research findings and the clinical considerations discussed above place PE as an excellent candidate for dissemination in large systems such as the VA and the Army. There is a small pool of experts on treatment of PTSD related to military trauma and even fewer experts with experience in disseminating EBT within large government systems. Efforts to disseminate PE have been spearheaded by the developer of PE, [name] who has worked closely with the VA for more than a decade, and with the Army and the DoD for the past 3 years. [name] is a world leader in research on EBT for PTSD and has created a specific training model for PE and a team that is experienced in implementing it. These resources will be used in the proposed research.

The Challenge of Disseminating Evidence-Based Treatment

At present, most people who suffer from PTSD do not receive evidence-based treatment (e.g., Kessler, Sonnega, Bromet, Hughes, & Nelson, 1995; Kulka et al., 1990), primarily because the availability of professionals who practice EBTs for PTSD is woefully limited (e.g., Becker et al.,2004; van Minnen et al., 2010). Accordingly, despite the well-documented effectiveness of PE and its recommendation in numerous practice guidelines, relatively few mental health providers deliver PE (Rosen et al., 2004; van Minnen et al., 2010). This state of affairs is not unique to PE; studies have documented insufficient use of exposure therapy in the treatment of other anxiety disorders (Freiheit, Vye, Swan, & Cady, 2004), and low rates of EBT delivery in general (Goisman, Warshaw, & Keller, 1999; Jameson, Chambless, & Blank, 2009).

The primary reason for the large discrepancy between the high efficacy of PE and its low utilization for PTSD patients is lack of adequate training in PE or other EBTs. Becker et al., (2004) surveyed psychologists to examine the extent to which providers were trained in, and used PE with their PTSD patients. The vast majority of providers reported no or modest experience in treating PTSD, and only a small minority had extensive experience treating this disorder. A minority of the providers reported that they had some training in PE, and even fewer reporting utilizing PE. Inadequate training was the single largest reported cause of not using PE. It follows that in order to increase the use of PE, providers need to receive effective training.

There is growing body of research indicating that EBTs can be effectively disseminated. Since 1995, there have been systematic and extensive efforts to transport PE from academic centers to community clinics in Philadelphia (Foa et al., 2005) and abroad (e.g., Israel, Japan, China). The most ambitious project involved disseminating PE throughout the VA system in the US as part of the VA Central Office initiative to disseminate EBTs for several mental health disorders. The project has been quite successful: even before the implementation of a systematic plan to accommodate the use of PE in the VA, 45% of providers who were trained are using PE regularly with their PTSD patients (Karlin et al., 2010). The aim of this program was to provide the VA with sustainable capacity to train and supervise their mental health practitioners in the delivery of EBTs for PTSD without the need for ongoing outside instruction. In 2009 alone, a total of 968 clinicians were trained to provide PE within the VA system, and an additional 269 were trained outside of VA in coordination with the PE role out initiative. Thus, top-down dissemination strategies appear to be an effective way to train a large number of mental health professionals in a short period to deliver PE for PTSD. Other research on disseminating PE has shown that community-based clinicians can be trained to effectively implement PE for PTSD when provided with comprehensive training that includes expert consultation (Foa et al., 2005, Karlin et al., 2010).

How Can We Increase Providers Use of PE Most Effectively?

One feature of the VA training program that is thought to contribute considerably to the effectiveness of the dissemination is the implementation of comprehensive consultation (i.e., supervision) on two PTSD cases after a 4-day workshop on how to deliver PE. Indeed, a survey of VA providers found a significant increase in self-confidence in delivering PE and in anticipated benefits from PE, and a significant decrease in anticipated problems in delivering PE from post-workshop to post-consultation (Ruzek, Schnurr, Vasterling, & Friedman, 2011). Indeed, the rationale for including consultation on two cases as part of the training program is the hypothesis that the support and guidance provided by an expert PE consultant is critical in promoting the confidence providers need in order to adopt PE into their practice and to ensure that the skills and techniques learned during the workshop are implemented correctly. Evidence in support of this hypothesis comes from our own experience training US Army providers in PE, as well as from studies examining different training models for evidence-based treatments. Between 2007 and 2009, we provided 19 PE workshops to over 600 providers who treat active military personnel in the Army. In contrast to the PE training in the VA, the Army training plan did not require consultation following the 4-day workshop, and therefore systematic supervision was not provided. Subsequent efforts to engage previously trained providers in a refresher workshop and local consultant trainings prove futile. These efforts revealed that very few providers who participated in the PE workshops systematically utilize this treatment in their practice with their PTSD patients.

The Critical Role of Consultation in Changing Providers Use of PE

Research on disseminating other EBTs clearly suggests that supervision plays an important role in successfully implementing EBTs among mental health professionals. For example, studies of Motivational Interviewing (MI) for substance abuse have demonstrated that training via workshops alone yields limited increased proficiency in delivering MI (Baer et al., 2004; Miller & Mount, 2001), whereas the addition of case consultation increased provider MI proficiency over training via workshop only (West, DiLillo, Bursac, Gore, & Greene, 2007). In another study 140 licensed substance abuse providers were randomized to one of five training conditions, and assessed MI proficiency at pre-training, and for up to a year post-training. All training conditions were superior to the waitlist condition; however, those who received case consultation in addition to a workshop showed greater improvement than did those who received only a workshop. Furthermore, although those in the workshop-only condition showed immediate improvement in proficiency at post-training, there was a reversal of gains by the 4-month follow up, whereas those who received consultation maintained high levels of proficiency throughout the 1-year follow-up period (Miller, Yahne, Moyers, Martinez, & Pirritano, 2004). These results strongly suggest that post-workshop case consultation is critical in order to ensure adoption of newly learned skills to clinical practice.

Although workshops and one-time trainings may increase provider knowledge and behavior to some extent (Henggeler et al., 2008), such brief training does not appear to raise provider competence or treatment fidelity to recommended levels (Sholomskas et al., 2005), and any demonstrated gains may be temporary (Miller et al., 2004). These findings are extremely troubling because high levels of treatment fidelity and provider competence have been linked to superior patient outcomes for numerous EBTs (e.g., Hogue et al., 2008; Feeley, DeRubeis, & Gelfand, 1999; Schoenwald, Carter, Chapman, & Sheidow, 2008). Thus, any system that aims to improve patient outcomes by implementing EBTs will need to carefully attend to the training model it selects.

Extended training that includes case consultation requires a significantly greater investment of resources than does more standard training such as a one-time workshop. The advantages of a workshop-only training model are that providers can complete the training in a few days and it requires relative little investment (in terms of time and money) from providers and leadership. However, if the workshop-only training model does not effectively change provider behavior, then not only is the investment wasted, but more important, the goal of increasing access to effective and efficient treatment among soldiers suffering from PTSD will remain unrealized.

What Kind of Training is Needed to Maximize Providers’ Use of Prolonged Exposure?

It is imperative that EBTs for PTSD be disseminated in military mental health clinics to meet the growing demand for effective and efficient treatment for PTSD in a timely manner. Moreover, the training should be conducted in a manner that will ensure sustainability of implementation and maintenance of treatment quality and adherence. As noted above, there is considerable evidence to suggest that without additional case consultation, there is minimal impact of stand-alone training workshops on provider behavior. However, providing post-workshop case consultation is costly and is limited by the availability of experts to provide extended supervision. Thus, it is important to determine whether the Extended PE training (which includes a workshop + consultation on two cases) is superior to the Standard PE training (i.e., workshop without consultation, given that it is a more costly, resource-intensive approach. This proposal addresses the question of what training model optimizes the success of disseminating and implementing effectively the use of empirically supported treatments for PTSD in the Army by examining the outcome of two PE training models.

